2.4 Pentoxifylline (Trental**®**)

2.4.1 Description (adapted from the package insert for Pentoxifylline)

Pentoxifylline extended-release tablets for oral administration contain 400mg of the active drug and the following inactive ingredients: D&C Red No. 27 Aluminum Lake or FD&C Red No. 3, hypromellose USP, magnesium stearate NF, polyethylene glycol NF, povidone USP, talc USP, titanium dioxide USP, and other ingredients in a controlled-release formulation. Pentoxifylline is a tri-substituted xanthine derivative designed chemically as 1-(5-oxohexyl)-3. 7-dimethylxanthine that, unlike theophylline, is a hemorrheologic agent, i.e. an agent that affects blood viscosity. Pentoxifylline is soluble in water and ethanol, and sparingly soluble in toluene. The molecular formula is C13H18N4O3 and its molecular weight is 278.31.

- - 1. Clinical Pharmacology

Mode of Action

Pentoxifylline and its metabolites improve the flow properties of blood by decreasing its viscosity. In patients with chronic peripheral arterial disease, this increases blood flow to the affected microcirculation and enhances tissue oxygenation. The precise mode of action of pentoxifylline and the sequence of events leading to clinical improvement are still to be defined. Pentoxifylline administration has been shown to produce dose-related hemorrheologic effects, lowering blood viscosity, and improving erythrocyte flexibility. Leukocyte properties of hemorrheologic importance have been modified in animal and *in* *vitro* human studies. Pentoxifylline has been shown to increase leukocyte deformability and to inhibit neutrophil adhesion and activation. Tissue oxygen levels have been shown to be significantly increased by therapeutic doses of pentoxifylline in patients with peripheral arterial disease.

Pharmacokinetics and Metabolism

After oral administration in aqueous solution pentoxifylline is almost completely absorbed. It undergoes a first-pass effect and the various metabolites appear in plasma very soon after dosing. Peak plasma levels of the parent compound and its metabolites are reached within 1 hour. The major metabolites are Metabolite I (1-[5-hydroxyhexyl]-3, 7-dimethylxanthine), and Metabolite V (1-[3-carboxypropyl]-3, 7-dimethylxanthine), and plasma levels of these metabolites are 5 and 8 times greater, respectively, than pentoxifylline. Following oral administration of aqueous solutions containing 100 to 400mg of pentoxifylline, the pharmacokinetics of the parent compound and Metabolite I are dose-related and not proportional (non-linear), with half-life and area under the blood-level time curve (AUC) increasing with dose. The elimination kinetics of Metabolite V are not dose-dependent. The apparent plasma half-life of pentoxifylline varies from 0.4 to 0.8 hours and the apparent plasma half-lives of its metabolites vary from 1 to 1.6 hours. There is no evidence of accumulation or enzyme induction (Cytochrome P450) following multiple oral doses.

Excretion is almost totally urinary; the main biotransformation product is Metabolite V. Essentially no parent drug is found in the urine. Despite large variations in plasma levels of parent compound and its metabolites, the urinary recovery of Metabolite V is consistent and shows dose proportionality. Less than 4% of the administered dose is recovered in feces. Food intake shortly before dosing delays absorption of an immediate-release dosage form but does not affect total absorption. The pharmacokinetics and metabolism of pentoxifylline have not been studied in patients with renal and/or hepatic dysfunction, but AUC was increased and elimination rate decreased in an older population (60-68 years) compared to younger individuals (22-30 years).

After administration of the 400 mg extended-release pentoxifylline tablet, plasma levels of the parent compound and its metabolites reach their maximum within 2 to 4 hours and remain constant over an extended period of time. Co administration of pentoxifylline tablets with meals resulted in an increase in mean Cmax and AUC by about 28% and 13% for pentoxifylline, respectively, Cmax for Metabolite 1 also increased by about 20%. The extended-release of pentoxifylline from the tablet eliminates peaks and troughs in plasma levels for improved gastrointestinal tolerance.

2.4.3 Indications and Usage

Pentoxifylline is indicated for the treatment of patients with intermittent claudication on the basis of chronic occlusive arterial disease of the limbs. Pentoxifylline can improve function and symptoms but is not intended to replace more definitive therapy, such as surgical bypass, or removal of arterial obstructions when treating peripheral vascular disease.

- - 1. Contraindications

Pentoxifylline should not be used in patients with recent cerebral and/or retinal hemorrhage or in patients who have previously exhibited intolerance to this product or methylxanthines such as caffeine, theophylline, and theobromine.

- - 1. Precautions
       1. General Precautions

Patients with chronic occlusive arterial disease of the limbs frequently show other manifestations of arteriosclerotic disease. Pentoxifylline has been used safely for treatment of peripheral arterial disease in patients with concurrent coronary artery and cerebrovascular diseases, but there have been occasional reports of angina, hypotension, and arrhythmia. Controlled trials do not show that pentoxifylline causes such adverse effects more often than placebo, but as it is a methylxanthine derivative, it is possible some individuals will experience such responses. Patients on warfarin should have more frequent monitoring of prothrombin times, while patients with other risk factors complicated by hemorrhage (e.g., recent surgery, peptic ulceration, cerebral and/or retinal bleeding) should have periodic examinations for bleeding including hematocrit and/or hemoglobin.

- - - 1. Drug Interactions

Although a causal relationship has not been established, there have been reports of bleeding and/or prolonged prothrombin time in patients treated with pentoxifylline with and without anticoagulants or platelet aggregation inhibitors. Patients on warfarin should have more frequent monitoring of prothrombin times, while patients with other risk factors complicated by hemorrhage (e.g. recent surgery, peptic ulceration) should have periodic examinations for bleeding including hematocrit and/or hemoglobin. Concomitant administration of pentoxifylline and theophylline-containing drugs leads to increased theophylline levels and theophylline toxicity in some individuals. Such patients should be closely monitored for signs of toxicity and have their theophylline dosage adjusted as necessary. Pentoxifylline has been used concurrently with antihypertensive drugs, beta blockers, digitalis, diuretics, antidiabetic agents, and antiarrhythmics, without observed problems. Small decreases in blood pressure have been observed in some patients treated with pentoxifylline; periodic systemic blood pressure monitoring is recommended for patients receiving concomitant antihypertensive therapy. If indicated, dosage of the antihypertensive agents should be reduced.

- - - 1. Carcinogenesis, Mutagenesis and Impairment of Fertility

Long-term studies of the carcinogenic potential of pentoxifylline were conducted in mice and rats by dietary administration of the drug at doses up to 450mg/kg (approximately 19 times the maximum recommended human daily dose (MRHD) in both species when based on body weight; 1.5 times the MRHD in the mouse and 3.3 times the MRHD in the rat when based on body surface area). In mice, the drug was administered for 18 months, whereas in rats, the drug was administered for 18 months followed by an additional 6 months without drug exposure. In the rat study, there was a statistically significant increase in benign mammary fibroadenomas in females of the 450mg/kg group. The relevance of this finding to human use is uncertain. Pentoxifylline was devoid of mutagenic activity in various strains of *Salmonella* (Ames test) and in cultured mammalian cells (unscheduled DNA synthesis test) when tested in the presence and absence of metabolic activation. It was also negative in the *in vivo* mouse micronucleus test.

- - - 1. Use in Pregnancy

Category C. Teratongenicity studies have been performed in rats and rabbits using oral doses up to 576 and 264 mg/kg, respectively. On a weight basis, these doses are 24 and 11 times the maximum recommended human daily dose (MRHD); on a body-surface-area basis, they are 4.2 and 3.5 times the MRHD. No evidence of fetal malformation was observed. Increased resorption was seen in rats of the 576 mg/kg group. There are no adequate and well controlled studies in pregnant women. Pentoxifylline should be used during pregnancy only if the potential benefit justifies the potential risk to the fetus.

- - - 1. Nursing Mothers

Pentoxifylline and its metabolites are excreted in human milk. Because of the potential for tumorigenicity shown for pentoxifylline in rats, a decision should be made whether to discontinue nursing or discontinue the drug, taking into account the importance of the drug to the mother.

- - 1. Adverse Reactions

Clinical trials were conducted using either extended-release pentoxifylline tablets for up to 60 weeks or immediate-release pentoxifylline capsules for up to 24 weeks. Dosage ranges in the tablet studies were 400 mg bid to tid and in the capsule studies, 200-400 mg tid. The incidence of adverse reactions was higher in the capsule studies (where dose related increases were seen in digestive and nervous system side effects) than in the tablet studies. Studies with the capsule include domestic experience, whereas studies with the extended-release tablets were conducted outside of the US. Few patients discontinued because of adverse effects.

Pentoxifylline has been marketed in Europe and elsewhere since 1972. The following have been reported spontaneously since marketing or occurred in other clinical trials with an incidence of less than 1%; the causal relationship was uncertain:

Cardiovascular-dyspnea, edema, hypotension.

Digestive-anorexia, cholecystitis, constipation, dry mouth/thirst.

Nervous-anxiety, confusion, depression, seizures.

Respiratory-epistaxis, flu-like symptoms, laryngitis, nasal congestion.

Skin and Appendages-brittle fingernails, pruritus, rash, urticaria, angioedema.

Special Senses-blurred vision, conjunctivitis, earache, scotoma.

Miscellaneous-bad taste, excessive salivation, leucopenia, malaise, sore throat/swollen neck glands, weight change.

A few rate events have been reported spontaneously worldwide since marketing in 1972. Although they occurred under circumstances in which a casual relationship with pentoxifylline could not be established, they are listed to serve as information for physicians: Cardiovascular-angina, arrhythmia, tachycardia, anaphylactoid reactions. Digestive-hepatitis, jaundice, increased liver enzymes; and Hemic and Lymphatic-decreased serum fibrinogen, pancytopenia, aplastic anemia, leukemia, purpura, thrombocytopenia.

2.4.7 Overdosage

Overdosage with pentoxifylline has been reported in pediatric patients and adults. Symptoms appear to dose related. A report from a poison control center on 44 patients taking overdoses of enteric-coated pentoxifylline tablets noted that symptoms usually occurred 4-5 hours after ingestion and lasted about 12 hours. The highest amount ingested was 80mg/kg; flushing, hypotension, convulsions, somnolence, loss of consciousness, fever, and agitation occurred. All patients recovered. In addition to symptomatic treatment and gastric lavage, special attention must be given to supporting respiration, maintaining systemic blood pressure, and controlling convulsions. Activated charcoal has been used to absorb pentoxifylline in patients who have overdosed.

2.4.8 Dosage and Administration

The usual dosage of pentoxifylline in extended-release tablet form is one tablet (400 mg) three times a day with meals. While the effect of pentoxifylline may be seen within 2 to 4 weeks, it is recommended that treatment be continued for at least 8 weeks. Efficacy has been demonstrated in double-blind clinical studies of 6 months duration.

Digestive and central nervous system side effects are dose related. If patients develop these effects it is recommended that the dosage be lowered to one tablet twice a day (800 mg/day). If side effects persist at

this lower dosage, the administration of pentoxifylline should be discontinued.

2.5 Study Rationale

Finding inexpensive and easily tolerated agents for the improvement of HIV-related endothelial dysfunction and cardiovascular disease risk is vitally important given the worldwide HIV epidemic that disproportionately affects those living in developing economies.

The literature strongly suggests that HIV is associated with an increased risk of cardiovascular disease. Untreated HIV is associated with an inflammatory vasculopathy comprised of increased leukocyte adhesion and upregulated MCP-1 and VCAM-1. Untreated HIV is also associated with increased serum levels of soluble VCAM-1 and impaired endothelial function. This suggests that inhibition in the leukocyte recruitment and adhesion pathway may improve endothelial function and potentially reduce the risk of future cardiovascular events.

In this trial, we will seek to confirm our preliminary results by conducting a placebo-controlled, randomized study of PTX given for 8 weeks in HIV-infected patients not requiring cART and with a CD4 cell count >350/µL (13 per group; total N=26). Because we wish to avoid the potential confounding effects of cART on FMD, choosing this CD4 count criterion will allow us to evaluate patients who do not require antiretroviral therapies per current treatment guidelines. We had considered performing a longer trial of PTX in this group of subjects to determine sustainability of FMD improvement. However, our primary goal is to determine if PTX truly improves FMD, which should be achieved with an eight week trial based on our pilot data. The less expensive eight week study period will also allow us to evaluate the efficacy of PTX without concern of a decline in CD4 counts over this short timeframe that would then require initiation of cART and contaminate our results. If PTX does indeed improve FMD over this short timeframe, then future studies of longer duration can be designed to determine the sustainability of endothelial function improvement with PTX. Moreover, these investigations may serve as a model for other chronic inflammatory conditions associated with increased cardiovascular risk (e.g. systemic lupus erythematosis, hepatitis C, diabetes, and chronic kidney disease).

3.0 STUDY DESIGN

3.1 Overview

The objectives for this study will be met by conducting a randomized, placebo-controlled trial to determine the effects of 8 weeks of PTX on FMD in HIV-infected subjects not requiring cART and without any other significant cardiovascular risk factors (see Schedule of Events below). Based on our pilot data, the eight week design will allow sufficient time to determine if PTX truly improves FMD while being short enough to avoid contamination of cART initiation in the event of a decline in CD4 cell count. The dose of 400mg three times per day is the same dose used in our pilot study.

A total of 26 subjects, 13 in each arm, will be randomized (see Sample Size Estimation below). Up to 50 potential subjects will be screened to achieve the target of 26 randomizations. Because our preliminary data suggest that the improvement in FMD with PTX does not depend on baseline FMD, we will not stratify or limit inclusion based on this latter variable.

There are no published data that suggest that remote use of antiretroviral therapy affects FMD in those not receiving cART. Thus, we will allow subjects to enroll if they have not received antiretrovirals for at least six months prior to screening as opposed to mandating that subjects be completely antiretroviral-naïve to be eligible. Such subjects are likely those who were given cART despite having higher CD4 counts and stopped due to side effects. The six month period was chosen to provide sufficient time to allow washout of their previous therapies and return to baseline immune and virologic states. This criterion matches what we used in our pilot experiments, will increase the potential subject pool, and will make the study more generalizable while not affecting the validity of the final results. We will adjust for previous cART use as a baseline variable in the final analyses.

We will also study peripheral blood markers of inflammation (sVCAM-1, IP-10) that were affected by PTX in our preliminary investigations. Other potential confounding variables, such as smoking status, insulin resistance, dyslipidemia, and waist-hip ratio, will also be measured and adjusted for statistically in the final analyses. Plasma, serum, and urine samples will also be frozen and archived at both the central repository as mandated under the RFA supporting this trial and at our site for future studies of interest.

3.2 Screening visits

If deemed eligible for screening, the subject will be approached (with permission/referral of the potential subject’s primary care provider) by either a study investigator or by an Infectious Diseases Research Clinic study nurse to enter the screening phase of the study. After written, informed consent is provided, a random study code number will be assigned to the subject to ensure confidentiality. This study code number will be used for laboratory transport and processing, result reporting, and data recording.

At this visit, the medical/medication history will be reviewed and a brief physical examination will be performed. Blood will be drawn to determine if the subject meets the laboratory eligibility criteria (see Eligibility Criteria). Urine pregnancy testing for female study volunteers of reproductive potential will also be performed. All screening tests will be performed at the Indiana Clinical Research Center. If the eligibility criteria are met, then the subjects will enter the clinical trial.

Because we recognize that many inflammatory markers have not been systematically studied in HIV-infected patients (e.g. IP-10), we will attempt to minimize variability in baseline levels of these markers by averaging results from samples taken at both screening and at baseline.

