1. CLINICAL AND LABORATORY EVALUATIONS

6.1 Schedule of Events

| **Evaluations** | **Screening** | **Study Visits** | | |
| --- | --- | --- | --- | --- |
| **-21 to -7 Day(s)** | **Week 0/**  **Entry** | **Week 4**  **Days 28-42** | **Week 8/Closeout**  **Days 56-70** |
| **Documentation of HIV Status** | X |  |  |  |
| **Medical History** | X |  |  |  |
| **Medication History** | X |  |  |  |
| **Concomitant Medications** |  | X | X | X |
| **Pentoxifylline/Placebo Dosing Modifications** |  | Anytime after entry based on adverse side effects | | |
| **Family History** |  | X |  |  |
| **Smoking History** |  | X |  |  |
| **Brief Physical Examination** | X | X | X | X |
| **Signs & Symptoms** |  | X | X | X |
| **Diagnoses** |  | X | X | X |
| **Adherence Questionnaire** |  |  | X | X |
| **Assessment of effective blinding** |  |  |  | X |
| **Height** |  | X |  |  |
| **Weight** | X | X | X | X |
| **Vital Signs** | X | X | X | X |
| **Waist/Hip Circumferences** |  | X | X | X |
| **Serum Creatinine** | X | X | X | X |
| **Calculated Creatinine Clearance** | X | X | X | X |
| **Liver Function Tests** | X | X | X | X |
| **Urine Pregnancy Test** | X | Whenever pregnancy suspected | | |
| **Urine Analysis** |  | X | X | X |
| **Hematology** | X | X | X | X |
| **CD4/CD8 cell counts and percentages** | X | X | X | X |
| **HIV-1 RNA Level (viral load)** |  | X | X | X |
| **Hepatitis B/C Serologies** |  | X |  |  |
| **PTX Levels** |  | X | X | X |
| **Whole blood for Advanced Flow Cytometry for Immune Activation (CD8+/CD38+/HLA-DR+ cells)** |  | X |  | X |
| **Frozen Serum/Plasma/Urine for Glucose, Insulin, Lipids, Albuminuria, Inflammatory and Endothelial Activation Markers** | X | X | X | X |
| **Frozen Plasma, Serum, & Urine for Future Studies** |  | X | X | X |
| **Brachial Artery Reactivity Testing** |  | X | X | X |

- 1. Definitions for Schedule of Events – Timing of Evaluations

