9.3.3 Secondary endpoints analyses

The secondary endpoints are the change in FMD at week 4 and the changes in plasma levels of MCP-1, sVCAM-1, IP-10, fasting lipids, HOMA-IR, CD4 cell count, activated CD8 cell proportions, and HIV-1 RNA level at week 8 from baseline. The secondary analyses will be in exploratory nature and will primarily be used for hypothesis generation. All the secondary outcomes will be analyzed by the same statistical methods as for the primary endpoint. To analyze how the changes in secondary outcomes correlate with changes in FMD, Spearman Rank correlation will be used.

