10.2.3 Potential Risks

- There are minimal risks to the subjects enrolled in the proposed research. The first is the potential loss of subject confidentiality. The second consists of the risks associated with blood drawing/needle sticks, which include pain, bruising, infection, and phlebitis. The amounts of blood to be drawn at screening and at each main study visit are 15cc (one tablespoon) and 45cc (three tablespoons), respectively. The total amount of blood to be obtained would be approximately 150cc (10 tablespoons) over at least 11 weeks. The primary risks associated with the use of pentoxifylline are gastrointestinal (nausea, vomiting, dyspepsia), flushing, and dizziness. PTX is a Pregnancy Category C drug and is found in breastmilk. There are no known or potential interactions with antiretroviral medications or commonly used therapies in the HIV-infected population. Nevertheless, we will carefully monitor CD4 counts and HIV-1 viral loads to assess for any potential worsening of immunologic/virologic status for those randomized to PTX during these studies and will be evaluated carefully by the DSMB. The primary risks associated with nitroglycerin administration as part of the brachial artery testing are headache and transient hypotension. NTG may also infrequently cause the sensation of flushing of the skin and rash. There may also be moderate pain associated with the inflation of forearm cuff as part of the brachial reactivity testing.
- The principal alternative to these procedures would be not to participate in the research.

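### CD4 is measured at both screening and Week 0, but the averaged baseline covers only inflammatory markers; the exploratory Week 8 CD4 comparison could use both values for a modest gain in precision.

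*Combined protocol and SAP*

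**What the plan says.** - Section 3.2 aims to reduce baseline variability in inflammatory markers, with IP-10 as the example, by "averaging results from samples taken at both screening and at baseline". Its reason is that many of these markers have been little studied in HIV infection. CD4 is not mentioned.
- The row "CD4/CD8 cell counts and percentages" in section 6.1 is marked at screening, Week 0, Week 4 and Week 8. Each subject therefore has two pre-treatment CD4 values.
- Section 9.3.3 lists as secondary endpoints the changes in "HOMA-IR, CD4 cell count, activated CD8 cell proportions, and HIV-1 RNA level at week 8 from baseline". They are analysed by the primary method, which section 9.3.2 defines as ANCOVA on change with the baseline value as covariate. Section 9.3.3 adds: "The secondary analyses will be in exploratory nature and will primarily be used for hypothesis generation".
- No section defines baseline CD4 for analysis. Section 3.2 separates screening from baseline, which points to Week 0. The medical history in section 6.3.2 uses baseline CD4 for a historical value.
- Section 4.1 applies the > 350/µL criterion to the screening value. Section 6.3.8.11 asks that CD4 be drawn at a consistent time of day, if possible, and sends screening safety results to the CRFs and the biostatisticians.
- Section 10.2.3 says: "we will carefully monitor CD4 counts and HIV-1 viral loads to assess for any potential worsening of immunologic/virologic status".

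**The concern.** A single CD4 count is a noisy measure of a subject's underlying level, and noise in the covariate weakens the baseline adjustment. The plan recognises this for inflammatory markers and averages two samples. For CD4 it schedules the same two visits but appears to use only one value. With about 10 completers per arm, the Week 8 CD4 comparison will have a wide interval, and a pre-treatment value that could narrow it is already collected. What is at stake is the precision of one exploratory comparison and a clear definition of its baseline.

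**Working it through.** **The plan's own figure.** There is no CD4 calculation to reproduce. The FMD sample size in section 9.2 does reproduce: SD of change = 2.21 × √(2 × (1 − 0.30)) = 2.615 (stated 2.62); two-sided t-test power with 10 per group, difference 3.5 and SD 2.62 is 80.6%; 10/0.8 = 12.5, rounded up to 13. This supplies the figure of 10 completers per arm.

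**Assumptions.** The CD4 variance and visit-to-visit correlation ρ are not in the documents. I take equal variances and one common ρ between visits, from 0.5 to 0.9. Residual variances are in units of the CD4 variance.

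- Week 0 alone as covariate (outcome Week 8 or change from Week 0): 1 − ρ².
- Mean of screening and Week 0 as covariate (outcome Week 8 or change from that mean): 1 − 2ρ²/(1 + ρ).
- Mean as covariate, but outcome change from Week 0: 2(1 − ρ) − (1 − ρ)²/(2(1 + ρ)).

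| ρ | Week 0 alone | Mean | Reduction | Mismatched pairing |
|---|---|---|---|---|
| 0.5 | 0.750 | 0.667 | 11% | 0.917 (+22%) |
| 0.7 | 0.510 | 0.424 | 17% | 0.574 (+12%) |
| 0.8 | 0.360 | 0.289 | 20% | 0.389 (+8%) |
| 0.9 | 0.190 | 0.147 | 22% | 0.197 (+4%) |

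The last column matters because change from baseline is the planned outcome. If only the covariate is swapped, the result is worse than the current plan.

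**With the screening cut.** I repeated the calculation with the screening value truncated at > 350, for pool mean/SD of 450/150, 500/150, 550/200 and 362/180. The 362 is the median in the untreated group of section 2.3.2; the rest is assumed. The reduction becomes 5–8% at ρ = 0.5, 10–14% at 0.7, 13–17% at 0.8 and 18–21% at 0.9. In standard error this is about 3% to 11%. Selection precedes randomization and is the same in expectation in both arms, so the between-arm contrast stays unbiased.

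**In cells/µL.** In simulations with 10 per arm, the cut, and an assumed mean of 500, the SE of the arm difference falls from 45.5 to 41.5 (between/within-subject SD 150/75) and from 60.5 to 55.7 (200/100). With 17 degrees of freedom (t = 2.11), the 95% half-widths go from about 96 to 88 and from about 128 to 118.

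**Within-arm change.** Because the screening value is selected to be high, an averaged baseline creates an apparent fall of ½(1 − ρ)σλ. Here σ is the CD4 SD, and λ = φ(a)/(1 − Φ(a)) with a = (350 − mean)/σ. For 500/150, λ = 0.288; at ρ = 0.7 the fall is ½ × 0.3 × 150 × 0.288 = 6.5 cells/µL. Over ρ = 0.5 to 0.9 it is about 2 to 16 for pool means of 450 to 550, and about 7 to 34 for 362/180. Week 0 alone has no such artefact.

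**Noisier screening value.** If screening error variance is f times that at Week 0, the mean carries (1 + f)/4 of the Week 0 error variance. Before truncation, averaging therefore helps only while f < 3. With the cut, for pools 500/150 and 362/180, a screening error SD 25% larger leaves a reduction of about 3–14%, and 50% larger about 1–6%.

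**The case against.** The strongest reply is that the plan contains no error. Section 3.2 gives a reason specific to little-studied inflammatory markers, and CD4 is a routine count with its own time-of-day control. The endpoint is exploratory, the gain rests on assumed correlations, and a half-width near 90 to 120 cells/µL remains imprecise either way. All of this stands, and it makes the point an optional refinement. It does not remove the gain, nor the need to say which value is the CD4 baseline.

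The quality of the screening draw is also a fair challenge. Section 3.3 specifies fasting morning samples at main visits; section 3.2 does not for screening. The gain shrinks accordingly.

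The cut at 350 is not a valid objection to the between-arm analysis. It does count against an averaged baseline for within-arm change.

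A reader might go further in three ways that the documents do not support:

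- **That this ANCOVA is the planned safety check on CD4.** Section 10.2.3 describes monitoring and DSMB evaluation, and section 10.3.2.5 individual CD4 checks when signs appear. Neither refers to the ANCOVA.
- **That the screening value is discarded.** It is recorded and forwarded. Its absence from the analysis is inferred from the plan's silence.
- **That the CD4 covariate in the primary FMD model should change too.** No gain is shown there. Section 2.3.2 found no significant correlation between FMD and CD4 in untreated subjects, and section 9.3.2 drops covariates without a significant association.

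**Conclusion.** The point holds as a minor precision gain for one exploratory endpoint. Using both pre-treatment CD4 values as the averaged covariate, with a matching outcome, reduces residual variance by about 5% to 21% and the standard error by about 3% to 11%. This assumes correlations of 0.5 to 0.9, equal visit variances and the > 350 screening cut; the gain is smaller if screening is noisier, and could vanish if it is much noisier. The direction is secure when the two visits are of similar quality; the size is not, because the documents give no CD4 variability. The primary FMD analysis, the sample size of 26 and individual safety monitoring are untouched. Viral load cannot benefit, because no screening HIV-1 RNA is scheduled.

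**What to change.** In section 9.3.3, define the between-arm CD4 analysis as ANCOVA with the Week 8 CD4 value as outcome and the mean of the screening and Week 0 values as covariate. Change from that mean is an equivalent outcome and gives the same treatment estimate. State that change from Week 0 must not be paired with the averaged covariate. Keep Week 0 alone as the reference for descriptive within-arm change and for individual review. In section 6.3.8.11, make clear that the time-of-day rule includes the screening draw. Leave the CD4 covariate in section 9.3.2 as it is.

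The cost is a few sentences, with no new samples or visits. The described change (from Week 0) and the analysed contrast will use different baselines, so tables must label which is which.
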